## Abstract

**Background/Objectives**: Disorders of gut–brain interaction (DGBI), characterized by chronic abdominal pain and significant disability, affect 15–20% of children and adults and continue into adulthood in ~60% of cases. Costs for adults reach USD 30 billion per year, yet effective management strategies are elusive. Studies support using cognitive behavioral therapy (CBT), but abdominal pain only improves in ~40% of patients. Dietary management (low FODMAP diet; LFD) has also shown promise but it is effective in only a similar percentage of patients. Studies suggest that biologic factors (biomarkers) contribute to CBT response. Similarly, gut microbiome composition appears to influence abdominal pain response to the LFD. However, no previous CBT trials in children or adults have measured these biomarkers, and it is unclear which patients respond best to CBT vs. LFD. **Methods**: Children aged 7–12 years with DGBIs (*n* = 200) will be categorized as having/not having Autonomic Nervous System imbalance and/or abnormalities in gut physiology. We will randomize these children to either CBT or a LFD to compare the effectiveness of these treatments in those with/without abnormal physiologic biomarkers. We hypothesize that CBT will be more effective in those without abnormal physiology and LFD will be more effective in children with abnormal physiology. Primary outcome measures include the following: (1) Symptom improvement (abdominal pain frequency/severity) and (2) improvement in health-related quality of life. **Conclusions**: This innovative multidisciplinary study is the first to identify physiological characteristics that may moderate the response to two different management strategies. Identification of these characteristics may reduce the burden of these disorders through timely application of the intervention most likely to benefit an individual patient.

## 1. Introduction

Disorders of gut–brain interaction (DGBI), also known as functional gastrointestinal disorders, are a group of disorders characterized by chronic gastrointestinal (GI) symptoms with an absence of underlying pathophysiology [1,2]. DGBI are classified based on symptom-based Rome IV criteria [3] and include pediatric disorders such as irritable bowel syndrome (IBS), functional abdominal pain (FAP), and functional dyspepsia (FD). These disorders are associated with chronic abdominal pain ranging from mild to severe (often with significant disability), altered stooling pattern, and psychological characteristics (including anxiety, depression, and impaired health-related quality of life) [4,5,6,7]. Additionally, pathophysiology (e.g., impaired gut barrier function, low-grade mucosal inflammation) appears to contribute to these disorders [8].

DGBI affect up to 15–20% of school-age children and adults worldwide [9,10]. Childhood DGBI continue into adulthood in many cases [11]. Despite the ubiquity of DGBI and the tremendous associated economic, social, and emotional burdens, widely effective treatment strategies have been elusive, in part because the definitions of the disorders have changed over time, are symptom-based, and are open to interpretation [12,13,14,15,16]. Thus, studies are needed to determine which pathophysiology and psychosocial factors contribute most to treatment response (or its lack) to a specific intervention. Additionally, identifying factors contributing to symptoms and how they may interact is central to the development of interventions to reduce or alleviate pain and disability, and potentially prevent or ameliorate the progression of these disorders into adulthood [13].

### 1.1. Altered Autonomic Nervous System (ANS) Function

The sympathovagal balance of the ANS plays a major role in regulating GI function including motility, secretion, and gut barrier function [17,18,19]. It has been hypothesized that alterations in the balance of sympathetic and parasympathetic functions, as measured by heart rate variability (HRV) input, contribute to abdominal pain/discomfort, constipation and diarrhea in DGBI [20]. Our group has shown a relationship between decreased HRV and increased depression in children with DGBI; however, it is unclear whether a relationship between HRV in response to CBT exists in children and/or adolescents with FGIDs [21,22,23].

### 1.2. Role of Diet

Studies have shown that 70–90% of children and adults with DGBI state that foods exacerbate their GI symptoms [24,25,26]. Fermentable oligosaccharides disaccharides and polyols (FODMAPs) are poorly absorbed and increase intestinal gas and/or induce an osmotic effect believed to be responsible for provoking symptoms. Data suggest that certain FODMAP sugars also can increase gut permeability and cause gut mucosal inflammation, or increase serum proinflammatory cytokines in IBS [27,28,29,30,31].

The LFD is a dietary intervention that restricts FODMAP dietary intake and has been shown to improve symptoms in adults and children with DGBI [32,33,34,35]. Pain remits within a few days of starting an LFD, with ~50% of pediatric and adult patients ultimately responding [35,36,37,38]. Our team has found that a diet eliminating a number of FODMAP foods in children with IBS resulted in only 30% of 113 children having a ≥50% improvement in abdominal pain frequency [39]. Importantly, psychosocial factors in both our randomized, double-blind FODMAP and fiber supplementation trials did not predict response [36,39].

### 1.3. Altered GI Microbiome Composition

Studies also suggest that the composition of the GI microbiome differs between DGBI patients and healthy individuals [40,41]. In a small group of children with IBS (*n* = 22), composition was related to severity of abdominal pain symptoms; this parallels findings in adults with DGBI [40,41,42,43,44,45,46,47]. Visceral hyperalgesia is a common finding in children and adults with DGBI that may be related to GI microbiome composition via the upregulation of immune responses, which, in turn, can increase gut permeability. Gut inflammation, the degree of which can be modified by gut bacteria and which can also be gender-dependent, can affect the function of smooth muscle and enteric nerves, resulting in dysmotility [48,49,50,51,52]. These data underscore the potential contribution of the GI microbiome not only to abdominal pain but also to other gut alterations (increased GI permeability and inflammation) found in some patients with DGBI. However, discrepancies exist among studies as to the strength of the relationship between symptoms (abdominal pain, bowel pattern) and differences in the gut microbiome. Thus, the links between microbiome signatures and symptoms of DGBIs remain to be fully elucidated.

The potential relationship between gut microbiome composition and responsiveness to treatment is varied; CBT has received scant attention in the adult and pediatric literature [53,54]. For example, Chumpitazi et al. showed in children that baseline microbiome composition predicted response to an LFD, as well as to a challenge with the FODMAP fructan [55,56]. Discrepancies among studies investigating the potential relationship between gut microbiome composition, symptoms, and psychological distress and response to treatment (CBT, LFD) are likely due to differences in patient populations, bacterial sequencing methodology, and the data analytic approaches used.

### 1.4. Psychosocial Factors

Psychosocial factors have long been felt to be an important contributor to childhood/adult DGBIs. Stress and parental modeling and responses have been proposed to account for the maintenance of pain and disability [57,58,59]. Parental and child cognitions about the origin, severity and controllability of the disorder (e.g., catastrophizing) in particular have been associated with increased pain severity and disability, suggesting that when parents and children perceive pain to be uncontrollable and threatening, the child likely will have worse outcomes [60]. Our novel observation that psychosocial factors are greater in children with DGBI who have normal vs. increased gut permeability supports the idea that gut pathophysiologic changes and psychosocial factors may provoke symptoms independently. To permit appropriately targeted DGBI interventions, these data highlight the critical need to investigate in individual patients whether pathophysiologic changes are present, and if so, whether they exist independently or are interactive with psychological factors.

### 1.5. Use of Cognitive Behavioral Therapy (CBT)

Meta-analyses of adult and pediatric studies support the use of cognitive behavioral therapy (CBT) and associated modalities as our best strategy to treat DGBI pain [61,62,63]. CBT is thought to improve patient pain reports, distress and function by altering dysfunctional cognitions and increasing patient involvement in activities through behavioral management, such as decreasing positive consequences for illness behaviors and increasing support for wellness behaviors and the use of coping strategies (e.g., relaxation and distraction). However, little is known about which patients are more likely to respond and which others likely require different management (e.g., dietary management, probiotics) [64,65].

In adults and children, abdominal pain only improves in ~40% of patients with CBT, in some cases delaying/supplanting more targeted management [66]. A recent Cochrane meta-analysis demonstrated that CBT was an effective treatment for reducing pain intensity in children with DGBI (OR 5.67, 95% CI 1.18–27.32), with more data supporting this management strategy than for other psychosocial interventions [67]. However, there was a dearth of follow-up at 3 months [67]. These findings match those from a previous systematic review [62]. The Cochrane meta-analysis, as well as one by Fisher et al., found insufficient evidence for an effect of CBT on disability [67,68]. Such findings have led to recommendations for research in pediatric patients to further establish the efficacy of CBT for non-pain outcomes such as disability, and to test CBT efficacy delivered via other change agents (i.e., parents) [61].

Our group has developed and tested an intervention for children with DGBI and their parents focused on modifying child and parent cognitions and behavioral responses to pain behaviors, with resulting reductions in child GI symptoms and improvements in functioning (i.e., fewer missed school days) [69]. A mediation analysis suggested that changes in child/parental cognitions and parental responses to their child’s pain mediated these positive outcomes. Thus, we conducted a subsequent study demonstrating that an intervention delivered via telephone to parents alone also was effective in improving child functioning [70]. In other studies, disability (including school absences/healthcare utilization) has been shown to be influenced by coping, independent of pain level, and coping (catastrophizing) has been found to mediate CBT response [71,72,73].

Our own work and that of others shows that some effects are durable for at least 12 months [74,75]. However, we found that ~50% of participants in our initial RCT of CBT for DGBI showed a <10% improvement in abdominal pain or other GI symptoms at 6-month follow-up [69,74]. While this may be due, in part, to the fact that baseline levels of pain and symptoms were overall relatively low, this finding also suggests the possibility that a lack of treatment response to CBT could occur in a subset of children with DGBI related to one or more physiological abnormalities described above—a question this study will address. It may be that modest effect sizes in this and other studies of CBT for DGBI are partly the result of unrecognized GI pathophysiology limiting CBT effectiveness—a knowledge gap this study seeks to fill [64]. Failure to recognize the presence of these physiological factors could result in delays in initiating other potentially effective therapies (e.g., dietary management). Given that factors consistently predictive of response to CBT for pediatric abdominal pain have not been identified [76], studies such as the one proposed here that simultaneously examine psychosocial factors and pathophysiology are likely to provide novel insight into predictors of CBT response.

### 1.6. Summary

The use of biomarkers to distinguish those who would benefit from CBT vs. more from an alternative treatment is innovative, and could assist healthcare providers in selecting appropriate treatment for an individual patient, particularly as there are no drugs clearly shown to be effective for treating pediatric DGBI [77]. The widely accepted premise that etiology and/or maintenance of DGBI is best understood within a biopsychosocial model incorporating interactions among biological/psychological/environmental factors offers potential direction in treatment decisions [78,79]. In an individual patient, one or more physiologic factors (e.g., gut dysbiosis, barrier dysfunction) may contribute more to symptom generation than in another patient with only psychosocial distress, yet studies have paid insufficient attention to physiologic factors potentially predicting poor response to CBT; a critical gap [65,80]. To personalize treatments, data are needed delineating factors affecting responsiveness.

## 2. Materials and Methods

### 2.1. Trial Design

The proposed study is a randomized controlled trial with a two-group design (CBT vs. LFD). Figure 1 shows the study recruitment flow and condition allocation.

### 2.2. Study Setting

Children with DGBI will be recruited through the Texas Children’s Hospital Pediatric Gastroenterology, Hepatology, and Nutrition Service (4 nurse practitioners, 37 physicians) and the Texas Children’s Hospital Primary Care Associates (TCPA), which is the nation’s largest group of general pediatricians (50 nurse practitioners, 205 physicians) at 50 locations throughout the Houston metropolitan area.

### 2.3. Eligibility Criteria

The sample will include 200 children with DGBI. Complete inclusion and exclusion criteria are presented in Table 1.

### 2.4. Sample Size

The sample size will be 100 subjects per treatment group (i.e., 200). Table 2 shows how power depends on effect size, which is unknown, and also the fraction of subjects in the abnormal biomarker subgroup. Power for detecting an interaction should be good if the effect size is ≥0.9. In our prior study delivering CBT to adults with DGBI and measuring biomarkers (*n* = 85), the effect sizes observed were 1.12 for LF/HF ratio and 0.76 for high-frequency HRV [81]. Given our proposed sample size is >2-fold greater than in our previous studies and 30% of children with DGBIs have increased gut permeability [8], we should be able to detect potential differences between groups.

### 2.5. Recruitment

Children with DGBI will be recruited through the Texas Children’s Hospital Pediatric Gastroenterology, Hepatology, and Nutrition Service and the TCPA, as described above. Thus, the profile of the local population will be reflected in the study sample (see Enrollment Report). Our findings should be generalizable to the real-world situation as we will recruit from primary and tertiary care. IRB approval will be obtained. Subjects will be identified by reviewing billing records for ICD-10 codes for abdominal pain and IBS (DGBIs). All medical charts will be reviewed by one of the principal investigators ([name]). Families will be invited to participate in a letter sent out by their nurse practitioner, pediatrician, or pediatric gastroenterologist. All healthcare providers are in the same academic practice, so there is full participation in referring children to the study. Once the letter is sent out, the research coordinators will call the family for additional screening using the questionnaire developed by the Pediatric Rome IV Working Group [3].

### 2.6. Randomization

Group allocation will be determined using a computer-generated algorithm with equal assignments to each study arm. Subjects will be stratified based on age (7–9 vs. 10–12), sex, baseline pain (mean pain frequency (≤50% of the rated intervals or >50% of the rated intervals, as reported on the baseline 2-week pain diary)), QOL, and presence/absence of abnormal physiological biomarkers.

### 2.7. Intervention

#### 2.7.1. Cognitive Behavioral Therapy (CBT)

Study treatments will be conducted by psychologists or master’s-level therapists with a minimum of 2 years of CBT postgraduate experience. They will receive at least 30 h of training in the manualized therapy prior to conducting treatment sessions. Training will consist of didactic presentations, modeling, role-playing by therapists, and corrective feedback, with repetition as needed. Therapists will be provided with a standardized protocol for each session. Treatment sessions also will be audio-recorded.

CBT treatment will be manualized and consist of a 60 min session conducted by phone once per week for 3 weeks. The number of treatment sessions was based on the successful outcomes of our previous studies and our commitment to developing treatments that are maximally accessible [69,70,81,82,83]. The intervention will be delivered to parents via telephone. Intervention strategies that involve children, such as at-home distraction or relaxation exercises, will be taught to children by their parents. Based on our work described above and that of others [69,84,85], the intervention has the following primary goals: Teaching parents a.) ways to differentially encourage, attend to and reinforce wellness behaviors (those behaviors incompatible with illness and disability) while decreasing attention to and reinforcement of illness behaviors related to abdominal pain; (b) more adaptive cognitive coping strategies and perspectives on their child’s pain, including reducing catastrophizing cognitions and threat appraisals regarding their child’s DGBI; (c) techniques for coaching their child to engage in cognitive-behavioral coping relaxation strategies, stress management and cognitive techniques (e.g., examining and altering self-talk); (d) how to model healthy responses to somatic symptoms; and (e) enabling parents to teach their children strategies such as relaxation training by providing parents audio-recordings to utilize with their children. Van Tilburg et al. has shown that guided imagery, a common relaxation technique applied within CBT, can be successfully delivered through audio-recordings to children with DGBI [86]. The intervention is specifically targeted to improve coping and management skills for symptoms, decrease healthcare utilization and functional disability, and improve QOL. Treatment fidelity—the extent to which a therapist uses interventions prescribed by a protocol [87]—will be closely monitored.

#### 2.7.2. Low FODMAP Diet Condition (LFD)

There are three phases in an LFD. (1.) Restriction phase: strict avoidance of high-FODMAP foods, and replacing them with low FODMAP alternatives; if symptoms improve, one can move to the next phase. (2.) Reintroduction phase: gradually reintroduce each FODMAP to determine which FODMAP(s) and at what doses trigger symptoms. (3.) Personalization phase: continued monitoring of symptoms with tailored diet for long-term adherence and nutritional adequacy [88,89,90].

The LFD will be administered by registered and licensed dietitians due to the risks of nutritional inadequacy and disordered eating. Parents will receive detailed instructions for following an LFD with recommendations for helping their children follow and adhere to the diet. They will be taught the definition of FODMAPs and how to identify and select low-FODMAP foods, and will be provided with tools they can use to help with diet compliance. Families will also be provided with recipes and a table detailing foods to avoid and foods allowed on the diet, as well as some low-FODMAP foods (such as gluten-free pasta and bread and low-FODMAP sauces) to help them get started. Recommendations will be tailored based on the child’s likes and dislikes, foods the family normally eats, and special circumstances (i.e., holidays and vacations). All 3 phases of the LFD (described above) will be implemented, with special focus on the elimination phase, in a similar fashion to other studies [91]. The dietitian will contact the family for approximately 1 h once a week for three weeks to check on the progress of following the diet, provide additional information as needed, and answer any questions. Thus, the CBT and low-FODMAP groups will have a similar degree of contact (once weekly for 1 h) with the study staff. As in the CBT group, sessions will be audio-recorded and reviewed for protocol consistency. Parents will complete a food diary at baseline and at post-treatment (while on the LFD; post-treatment food records will be used to determine adherence to the LFD). The Nutrition Data System for Research (University of Minnesota) will be used to analyze the food diaries. Based on our previous studies, compliance with the diet is >90% [36,38,92]. The children will have FODMAPs reintroduced gradually into their diet under the guidance of the dietitian, as is done clinically. Should a specific FODMAP appear to cause abdominal pain, the child may continue to exclude that food from their diet.

### 2.8. Outcomes

Primary outcomes are abdominal pain and QOL at 3 months. Secondary outcomes include pain and QOL at 6 months, healthcare utilization, missed school days, and sleep.

### 2.9. Study Timeline

The study timeline includes an enrollment period, baseline assessment, randomization, treatment, and 5 post-treatment assessment periods (immediately post-treatment, and 3,6,12, and 18-months post-treatment), as shown in Table 3. Specific measurements and timepoints are shown in Table 4.

### 2.10. Blinding

With the exception of study coordinators, therapists, dietitians, and statisticians, all other study staff will be blinded to treatment assignment. Blinding will be made possible through restricting access to participants’ treatment assignments in the study database only to staff whose role is to assign participants to interventions, contact participants throughout the intervention phase, deliver study treatments, or analyze results by treatment group. Study participants will also not be blinded to treatment.

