### 2.15. Statistical Methods

The primary outcome variables at 3 months after completing treatment will be mean number of pain episodes/week and QOL. An analysis of covariance model will be fit, with pain frequency and QOL as the outcome variables, and treatment group (CBT or LFD) and biomarker group (abnormal versus normal) as factors, using baseline pain frequency and QOL as covariates. The interaction between treatment group and biomarker group will be included in the model, and the test of this interaction term will be the primary test of interest. If this term is zero then the null hypothesis is true and the effectiveness of CBT relative to the LFD is the same in the two biomarker groups. If the interaction is significantly different from zero, the relative effectiveness of CBT versus the LFD differs between the two biomarker groups. A general overview of this analytic approach can be found in Figure S1 in the Supplementary Materials. We will test the effect of sex using the above-described analysis of covariance model, wherein sex will be used instead of biomarker group as a factor. Similar analyses will be done for the additional secondary outcome measures of healthcare utilization, missed school days, and sleep. We will examine pain and QOL trajectories. However, 3 months is specified as the primary outcome time because if the effect does not last until at least 3 months, it is less impactful clinically, and there will be fewer missing data at 3 than at 6 months.

Baseline pain frequency/QOL potentially could confound the interaction effect being tested—treatment effectiveness (improvement with CBT minus improvement with the LFD) may be greater for those with higher baseline pain frequency/lower QOL. If so, the interaction between treatment group and baseline pain frequency also will be included in the model.

Two approaches will be considered regarding missing data. The first uses a mixed model to analyze all three time points together. This allows some time points to have missing data, but still gives unbiased estimates if data are missing at random, conditional on the data that are not missing. The second will be multiple imputations, which imputes missing data based on the data not missing.

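### Statisticians are unblinded to analyze by arm, although coded arms would serve for the primary test and some analysis choices are still open

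*Protocol article*

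**What the plan says.** Section 2.10 names four unblinded roles: "With the exception of study coordinators, therapists, dietitians, and statisticians, all other study staff will be blinded to treatment assignment". Database access to assignments is limited to staff who assign or contact participants, "deliver study treatments, or analyze results by treatment group". Of families it says: "Study participants will also not be blinded to treatment". No coded-arm step is described.

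Section 2.15 sets the endpoints: "The primary outcome variables at 3 months after completing treatment will be mean number of pain episodes/week and QOL". It fits an analysis of covariance with treatment, biomarker group and their interaction, and says that "the test of this interaction term will be the primary test of interest". On missing data: "Two approaches will be considered regarding missing data". These are a mixed model and multiple imputation, and neither is named as primary. The section then allows that the treatment difference may vary with baseline level, and continues: "If so, the interaction between treatment group and baseline pain frequency also will be included in the model". It gives no criterion for that decision.

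Table 4 collects the PedsQL from both parent and child. Neither section 2.11.4 nor section 2.15 says which report is the primary QOL score.

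The Abstract states the expected direction: "We hypothesize that CBT will be more effective in those without abnormal physiology and LFD will be more effective in children with abnormal physiology".

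**The concern.** The stated reason for unblinding statisticians is that they analyze by arm. An analysis by arm needs to know which children were treated alike, not which treatment each group received. Families are unblinded and the primary outcomes are reported by children and parents. Coordinators, therapists and dietitians can hardly be masked, given their work. Statisticians are the one exempted role that could be.

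The hypothesis predicts a sign for the interaction. An analyst who knows the arms can see whether a given version of the model supports that prediction while some choices are still to be made. The treatment-by-baseline term is the clearest example, because the decision to include it rests on how the treatment difference behaves in the data. An analyst who sees only A and B cannot tell a favourable interaction from an unfavourable one. At stake is the credibility of the primary interaction result.

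**Working it through.** **1. The plan's own figures.** The point concerns a stated rule and has no figure of its own. The nearest one is Table 2, the power of the interaction test. The inputs are N = 200 with equal allocation (section 2.4), smaller biomarker fraction f, and effect size ES in within-group SD units. Alpha is not stated, so two-sided 0.05 is assumed.

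- SE = sqrt(4/(200f) + 4/(200(1-f))), in SD units
- Power = Phi(ES/SE - 1.96)
- For ES = 0.9 and f = 0.5: SE = sqrt(0.04 + 0.04) = 0.283; 0.9/0.283 = 3.18; Phi(3.18 - 1.96) = 88.9%. Table 2 says 89%.
- For ES = 0.9 and f = 0.33 and 0.25: 84.9% and 78.7%. Table 2 says 85% and 78%.

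All 15 cells reproduce within one point. Nothing in the formula depends on which arm is called which.

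**2. Does the primary test need the arm names?** Write the model as Y = b0 + b1·T + b2·B + b3·T·B + b4·baseline, with T the arm and B the biomarker group. Replacing T by 1 - T changes b3 to -b3 and leaves its standard error alone. The t statistic changes sign and the two-sided p-value does not move. A fit to one simulated data set of 200 gave t = 0.499 one way and -0.499 the other, with p = 0.618 both times. Coded arms are enough.

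**3. What do the open choices do, and does coding stop it?** An illustrative simulation used 6,000 null trials in each of two scenarios: the abnormal group's baseline equal to that of the normal group, or 0.5 SD higher. The assumptions, none of them from the documents, were 15% of 3-month data missing at random and a biomarker fraction of 0.33. Complete-case analysis and single stochastic imputation stood in for the plan's two missing-data methods. Each was run with and without the treatment-by-baseline term, giving four versions per outcome.

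| One outcome | Equal baseline | Baseline 0.5 SD higher |
|---|---|---|
| One fixed version, two-sided error | 5.7% | 4.8% |
| Smallest p of four versions | 9.9% | 9.5% |
| Favoured direction, one fixed version | 3.0% | 2.2% |
| Favoured direction, arms known, best version picked | 5.2% | 4.5% |
| Favoured direction, arms coded, smallest p picked | 5.2% | 4.5% |

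The last two rows agree. Selection on the p-value therefore works equally well with coded labels. What coding takes away is the ability to search only when the sign is welcome, or to soften a result when it is not. Single imputation treats filled-in values as observed, so part of the rise may come from the stand-in. The table shows a mechanism and is not an estimate for this trial.

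**The case against.** The strongest reply is that prespecification does the work, not masking. If a statistical analysis plan that is not shown fixes the missing-data method, the PedsQL reporter and the rule for the extra term, an unblinded analyst has little left to steer. An article may properly leave those details to such a plan. This largely stands, and it limits the weight of the point. It does not remove it, because the unblinding is a positive statement in section 2.10 and not a gap, and the reason given does not require it.

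Three further replies also stand in part:

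- Section 2.10 already blinds all other study staff and restricts access to assignments.
- Masking would be imperfect, since post-treatment food records are used to judge adherence to the diet (section 2.7.2) and could reveal the arm.
- Self-report by unblinded families is probably the larger source of bias, and coding does nothing about it.

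A reader might infer that unblinding the statisticians inflates the type I error of the primary test by some definite amount. The documents do not support that. They give no basis for the size of any shift, and the simulation shows no excess with known arms over coded ones when the smallest p-value is picked. A reader might also infer that the biomarker split could be redrawn once the arms are known. Section 2.6 makes biomarker status a stratification factor, so each child must be classified before allocation.

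**Conclusion.** The point holds as a cheap, minor improvement. Section 2.10 unblinds statisticians for a purpose that coded arms would serve, while section 2.15 as published leaves the missing-data approach open and ties one model term to observed treatment effects.

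No numerical excess error is claimed for the unblinding. Coding reduces choices driven by direction and protects only when the open choices are locked as well. Sample size, power and the test itself do not change. The weight of the point depends on whether an analysis plan that is not shown already fixes those choices. If it does, the remaining benefit is smaller.

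**What to change.** - In section 2.10, remove statisticians from the unblinded list for the primary analysis.
- Give them a dataset with arms coded A/B, without post-treatment diet and adherence variables and without session content.
- Let staff who already have access to assignments, and who do not analyze the data, hold the key.
- Before any outcome data by arm, even coded, are seen, lock three things: the missing-data method, the PedsQL reporter, and the rule for the treatment-by-baseline term.
- Run the primary models, then open the code.

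The cost is a change of protocol wording and a small data-handling step: a restricted export, with the diet data released later. It needs no more participants or procedures and, with the key held as above, no new staff. Masking may still fail in places, so the report should say whether it held up to the primary analysis.
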